**Abstract**

**Background:** Cervical cancer is the leading cause of cancer death in females in Madagascar. In this country, a large-scale screening of precancerous lesions with cytology is hardly possible, because of the lack of specialists and infrastructures. Visual inspection of the cervix with application of 5% acetic acid (VIA) is an inexpensive alternative but very subjective since it depends on the examiner’s experience. Mobile telemedicine is a very promising tool in order to assist non-expert health-care workers in rural area for cervical cancer screening.

**Objective:** To assess if Smartphone may assist health-care worker (on-site) and to evaluate the diagnostic reliability and accuracy of cervical examination with smartphone photos of VIA (D-VIA) compared with conventional VIA, for women testing positive for human papillomavirus (HPV).

**Material and method:** On-site health care workers will be trained in VIA. Prescreened HPV-positive women will be referred to VIA evaluation, during which digital images with a smartphone (D-VIA) will be taken for later evaluation by a VIA specialist in Geneva linked by telemedicine. Women with positive VIA results will be treated with cold coagulation if eligible. Histological results will be considered as gold standard. The results will be analyzed with Cohen’s kappa coefficient, Mcnemar’s test and Bonferroni’s adjustment for multiple comparisons to assess the performance of D-VIA.

**Expected results:** Based on the results of this project, we will develop an educational training and quality assurance program for health providers for VIA and so contribute to a scaling-up of cervical cancer control. An appropriate triage by VIA will reduce not only an excessive referral rate but also an excessive treatment delay, giving the possibility of a “screen (HPV), see (VIA/D-VIA), and treat” program in a single or two visits.

**Key words:** Cervical cancer; HPV; VIA; screening; smartphone; telemedicine

1. **Introduction**

Cervical cancer is the second most prevalent cancer in women Worldwide ([1](#_ENREF_1)). In Madagascar, there are about 1553 new cancer cases every year ([2](#_ENREF_2)) and, according to country statistics ([3](#_ENREF_3)), 1085 women died in 2010, which makes cervical cancer a leading cause of cancer death in females. In Western Countries, most of cervical cancer can be prevented through cytology-based or HPV screening, but for low-resource countries such as Madagascar, a large-scale screening of precancerous lesions with cytology is hardly possible, because of the lack of specialists and infrastructures.

In order to overcome barriers associated to cytology-based screening programs in low-resource countries, the World Health Organization (WHO) has recommended the use of visual inspection with acetic acid (VIA), since it is a low cost method, easy to perform and does not need specialized laboratory. Additionally, VIA allows reducing the time between when testing occurs and results are available, which allows women to be screened and treated in a single appointment (“see-and-treat approach”).

On the other side, a major drawback of VIA is subjectivity and reliability because of lack of training and expertise. The effectiveness of VIA as screening tool depends essentially from the training of the healthcare workers for diagnosis, appropriate referral and treatment of cervical pre-cancer and cancer in women living in rural Africa with limited access to care. Because the training determines the effectiveness of the VIA, it highlights the potential advantage to develop a strategy for facilitating training and supervision for novice healthcare professional working in areas where physicians are not available.

Digital imaging may offer a support for physician, but problems are that it needs digital cameras, which are expensive and require substantial field training to operate. New Smartphones appear to be an obvious choice for the development of these "next-generation" tools for digital image acquisition. Potential advantage of Smartphones is that it is “easy-use” device, allows immediate image capture and transmissions to expert via MMS in a real time for advice.

Mobile telemedicine is a very promising tool for cervical cancer screening in these countries. In view of growing applicability of this technology we will examine the feasibility, reliability and validity of a Smartphone for pre-cancer detection in low-resource countries.

1. **Objective**

Primary outcomes:

1) To evaluate if a Smartphone may assist health-care worker (in-site) for cervical cancer screening;

2) To evaluate how the expert at a distant location (off-site) may improve VIA results.

Secondary outcomes:

1) To assess the agreement between diagnoses based on the visualization of the cervix with the unaided eye, after the application of 5% acetic acid (control) during a patient clinical consultation and diagnoses for the same patient based on evaluation of Smartphone photos.

1. **Material and method**

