***Study procedure:***

An informed consent form will be obtained from each woman prior to participation in the study. A questionnaire will then be filled out, assessing socio-demographic data and clinical information. These questionnaires will be available in a secured online platform containing all data from all participants. This platform will be network connected with the University Hospitals of Geneva.

A trained on-site expert will visualize the cervix with a vaginal speculum and then acetic acid 5% will be applied for at least 30 seconds. Then, a conventional VIA is performed.

In addition, acquisition of an additional set of photography of the cervix than that routinely obtained during the exam (with a digital camera or a colposcope) will be performed. The additional digital images will be obtained with a Smartphone (Samsung Galaxy S5). Photographs will be done before and after application of acetic acid and Lugol. This will result in approximately three photos per woman and should yield very little discomfort for the women.

A university-based on-site expert will independently conduct another VIA evaluation, blinded to the health worker’s evaluation.

Biopsies of the cervix (on the four forties and the lesion if any) and endocervical curettage will be performed.

All photographs will be transmitted to University Hospitals of Geneva for expert analysis. This will be made by MMS, e-mail or via RAFT network. All the images will be stored in the online platform.

The “offsite” diagnosis will be transmitted to health care worker having conducted the “in-site” diagnosis and consensus will be discussed.

The on-site health worker and the on-site university-based expert will evaluate the stored digital images (D-VIA) three months after the initial visit, and blinded to their original evaluation.

Since correlation between cytology and histology is known to be poor ([4](#_ENREF_4)), a cervical smear will be done at the end of the procedure.

Subjects deemed to be VIA positive will be treated at the same visit with cold coagulation if eligible (see flowchart).

All photographs stored in the database will be later used for educational purposes.

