***Statistical analysis:***

Sample size: Based on previous studies in Ambanja (population of 28,468), Madagascar, we assume that the prevalence of CIN2+ lesions detected by D-VIA will be of 8% and of 4% by classical VIA interpretation. We have assumed 80% power at an alpha level of 0.05, using a 2-sided hypothesis. With this assumption, 1000 women will be needed.

Adequacy results: VIA and D-VIA results will be categorized as “satisfactory” (positive or negative) and “unsatisfactory”. Adequacy results (satisfactory or unsatisfactory) will be compared. Comparisons of percentages will be made between positive and negative VIA and positive and negative D-VIA. The McNemar’s test for comparisons and the Cohen’s kappa coefficient to measure reproducibility between VIA and D-VIA will be used.

Agreement results: Percentage of agreement will be calculated for each pair of on-site results and for distant D-VIA results by using McNemar’s test and adjust the p values with Bonferroni correction for multiple comparisons in order to overcorrect for Type I errors. Agreement of results will be also evaluated using Cohen’s kappa coefficient.

The following agreement results between assessors will be determined:

1) VIA results made by on-site health worker vs. distant expert D-VIA results

2) VIA results made by on-site expert vs. distant expert D-VIA results

3) VIA results made by on-site health worker vs. VIA results made by on-site expert

4) VIA results made by on-site health worker vs. on-site health worker’s D-VIA blinded results at 3 months

5) VIA results made by on-site expert vs. on-site expert D-VIA blinded results at 3 months

6) On-site health worker’s D-VIA blinded results at 3 months vs. on-site expert D-VIA blinded results at 3 months

7) On-site health worker’s D-VIA blinded results at 3 months vs. distant expert D-VIA results

8) On-site expert D-VIA blinded results at 3 months vs. distant expert D-VIA results

Accuracy: Sensitivities and specificities for the gold standard (cervical histology) will be obtained with the Smartphone diagnosis. Positive and negative predictive values will also be determined.

1. **Expected contribution**

Smartphone high-quality photographic technology has proven to be very useful in detecting pre- cancerous lesions on the cervix in a previous study that also took place in Madagascar.

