**Off site diagnosis**

**On site diagnosis**

**TELECONSULTATION**

**DIAGNOSIS CONSENSUS AND MANAGEMENT**

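### Primary outcome 1 asks whether the smartphone assists the on-site worker, but no planned analysis contains an assisted worker diagnosis

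*Protocol*

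**What the plan says.** The protocol's Objective section separates three questions. Primary outcome 1 is "To evaluate if a Smartphone may assist health-care worker (in-site) for cervical cancer screening". Primary outcome 2 is how a distant expert may improve VIA results. The secondary outcome is agreement, in the same patient, between diagnosis with the unaided eye and diagnosis from smartphone photographs. No endpoint or comparison is attached to primary outcome 1.

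Under Study procedure, acetic acid is applied at the visit. "Then, a conventional VIA is performed", and smartphone pictures are taken in addition. The Abstract says these images "will be taken for later evaluation by a VIA specialist in Geneva linked by telemedicine". The health worker and the on-site university expert "will evaluate the stored digital images (D-VIA) three months after the initial visit, and blinded to their original evaluation".

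The same section describes one route back to the worker: the off-site "diagnosis will be transmitted to health care worker having conducted the" on-site diagnosis, after which consensus is discussed. The flowchart in the Annexes has a teleconsultation box and a box for "DIAGNOSIS CONSENSUS AND MANAGEMENT".

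Statistical analysis lists eight pairwise agreement comparisons. The fourth is "VIA results made by on-site health worker vs. on-site health worker’s D-VIA blinded results at 3 months". A separate accuracy paragraph sets the smartphone diagnosis against histology.

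**The concern.** To learn whether a tool assists someone, one needs that person's decision without the tool and with it. Here the worker's decision without it is recorded at the visit. The worker's decision with it, whether by viewing the phone image or by hearing the distant expert, enters no analysis.

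The nearest substitute is comparison 4, which asks whether a photograph read alone gives the same answer as the eye. That is replacement, not assistance, and it also mixes the effect of the picture with three months of elapsed time. A photograph can be a poor replacement and a useful aid, or a good replacement that adds nothing. If the plan is followed exactly, the first-listed primary outcome ends without an answer, or with the answer to the secondary question presented as its own.

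**Working it through.** **1. Is there a figure to reproduce?** Not for this outcome. The only design figure, 1000 women, rests on assumed CIN2+ detection of 8% by D-VIA and 4% by VIA. That contrasts two methods, not an assisted with an unaided worker. The point is therefore checked by setting the text side by side.

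**2. Which worker diagnoses does the plan describe?** Study procedure attributes the first VIA to a trained on-site expert. It then has a university-based expert do a second VIA blinded to the health worker's evaluation, so I take the first VIA to be the health worker's.

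| Worker diagnosis | When | Assisted? | In an analysis? |
|---|---|---|---|
| Conventional VIA | At the visit | No | Yes: 1, 3, 4 |
| Stored photographs alone, blinded | Three months | No (photograph replaces eye) | Yes: 4, 6, 7 |
| Eye plus phone image | Not described | Yes | No |
| Consensus after off-site diagnosis | Not fixed | Yes | No |

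**3. The eight comparisons.**

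| No. | Pair | Assisted worker diagnosis? |
|---|---|---|
| 1 | Worker VIA v distant D-VIA | No |
| 2 | On-site expert VIA v distant D-VIA | No |
| 3 | Worker VIA v on-site expert VIA | No |
| 4 | Worker VIA v worker D-VIA, 3 months | No |
| 5 | On-site expert VIA v own D-VIA, 3 months | No |
| 6 | Worker D-VIA v on-site expert D-VIA, both 3 months | No |
| 7 | Worker D-VIA, 3 months, v distant D-VIA | No |
| 8 | On-site expert D-VIA, 3 months, v distant D-VIA | No |

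The worker's D-VIA appears in 3 of 8 (4, 6, 7), always at three months, and against the worker's own VIA in 1 of 8 (4). An assisted worker diagnosis of either kind appears in 0 of 8. Comparisons 1 and 7 show how far the worker agrees with the distant expert, not whether the worker's diagnosis improves. The accuracy paragraph names only the smartphone diagnosis and makes no assisted-against-unaided contrast.

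**4. Is the described assistance timed?** The Introduction speaks of real-time advice and the Abstract of later evaluation. Study procedure has eligible VIA-positive women treated at the same visit, while the flowchart links consensus with management. Together these do not say whether the consensus comes before or after the visit's decisions, and they need to be reconciled.

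**5. Could a later analysis plan repair this?** Not for the worker's call with the phone image: a reading not recorded at the visit cannot be recovered. The consensus could be analysed only if it is captured as data, and the protocol does not list it among the results to be compared.

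**The case against.** **Assistance may simply mean telemedicine.** The Abstract says mobile telemedicine is meant to help non-expert workers, the Introduction stresses sending images to an expert for advice, and the flowchart adds learning from the photographs over time. Nowhere is the worker's look at the worker's own picture called the intervention. This stands in part. A reader might infer that the protocol has no assistance step at all; it does have one, the returned diagnosis and the consensus. But on this reading, too, the assisted result is untimed and unanalysed. Outcome 1 would also largely merge with outcome 2, which the protocol lists separately.

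**Mapping outcomes to analyses can wait for a SAP.** True of the mapping, but not of data that must be collected at the visit.

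**The three-month gap has a purpose.** Agreed: with blinding, it limits recall. Comparison 4 is a sound reliability result and should stay.

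**A size might be attached, but the documents do not support one.** Assume 10% CIN2+ among 1000 women (not a protocol figure), so 100 cases. VIA detecting 4% of 1000 finds 40, and suppose photographs alone also find 40. Counting a woman positive if either reading is positive gives 40 + 40 - overlap: 40, 52 or 64 for overlaps of 40, 28 or 16. A reader might infer that comparison 4 hides a gain of 0 to 24 points. It does not:

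- Percentage agreement and kappa are planned and separate these cases. Within CIN2+, agreement = overlap + (100 - 80 + overlap), giving 100%, 76% and 52%. Chance agreement is 0.4 × 0.4 + 0.6 × 0.6 = 0.52, so kappa is 1.0, 0.5 and 0. Over all women, kappa also depends on false positives.
- The either-positive result can be computed from the worker's VIA, the worker's D-VIA and the biopsy, all already planned.
- The range is no bound. Zero overlap gives 80, a gain of 40, and an aided worker can also turn a correct positive into a negative.

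**Conclusion.** The point holds as a gap between question and measurement. Primary outcome 1 asks about assistance, and 0 of 8 comparisons, and no part of the accuracy analysis, contain an assisted worker diagnosis. This is true whether assistance means the worker viewing the phone image or receiving the distant expert's advice.

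It rests on two readings of the text: that outcome 1 differs from the secondary outcome because the protocol lists them apart, and that the first VIA at the visit is the health worker's. It does not show that the smartphone would or would not help, and no number of missed lesions follows from it. The agreement and accuracy results keep their value. The change should be made before recruitment, because one of the missing readings cannot be obtained afterwards.

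**What to change.** **Study procedure.** Have the worker record and lock the unaided VIA before any other result is disclosed. Then record, as research data only:

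- (a) the worker's call after viewing the phone images at the visit, before the on-site expert's or distant result is known;
- (b) the consensus diagnosis reached after the off-site result, with its date and time.

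Which result drives care stays as the protocol has it. The statements on when the off-site diagnosis and consensus occur should be reconciled.

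**Statistical analysis.** Define the analysis of primary outcome 1 as the paired comparison of the locked unaided VIA with (a) and with (b), each separately in women with and without CIN2+ on histology. The split matters because an aid may raise detection at the price of false positives. Keep comparison 4 as a reliability result, and state whether the new comparisons fall within the Bonferroni adjustment.

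**Cost.** One or two extra form fields and a few paired analyses on histology already planned; no added staff or procedures. Two drawbacks should be stated: call (a) will be anchored on the unaided call made moments earlier, and viewing the pictures at the visit may carry some memory into the three-month blinded reading used in comparisons 4, 6 and 7. The documents give no basis for sizing either effect.

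### Primary outcome 2, improvement of VIA by the distant expert, has no direct analysis: the post-teleconsultation consensus is in none of the planned comparisons

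*Protocol*

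**What the plan says.** The Objective section of the protocol lists two primary outcomes. The first is "To evaluate if a Smartphone may assist health-care worker (in-site) for cervical cancer screening"; the second is "To evaluate how the expert at a distant location (off-site) may improve VIA results". The single secondary outcome is agreement between unaided-eye diagnoses and "diagnoses for the same patient based on evaluation of Smartphone photos".

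Under Study procedure, the off-site reading goes back to the health worker who made the on-site one, and the "diagnosis and consensus will be discussed". The Flowchart (5.1) carries a teleconsultation box and a box labelled "DIAGNOSIS CONSENSUS AND MANAGEMENT".

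The Statistical analysis section introduces a list of eight pairs with "The following agreement results between assessors will be determined". The first pair is "VIA results made by on-site health worker vs. distant expert D-VIA results". A separate accuracy paragraph plans sensitivity, specificity and predictive values of the smartphone diagnosis against cervical histology. It names no other diagnosis and does not say which of the three photo readings is meant. The Abstract states the aim as reliability and accuracy of D-VIA relative to conventional VIA.

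On treatment, Study procedure says "Subjects deemed to be VIA positive will be treated at the same visit with cold coagulation if eligible".

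**The concern.** A primary outcome about improvement needs a before and an after: the worker's diagnosis without the expert, and the diagnosis once the expert has contributed. The protocol plans a step that yields the second of these, the consensus, but never says that it is recorded as a result and never analyses it.

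The planned agreement statistics show whether two readers differ. They do not show whether the worker's diagnosis became more often correct. A correct expert call that the worker does not accept brings no improvement, and an expert error that the worker adopts makes the result worse. If the consensus is not captured when it is reached, it cannot be reconstructed later, whatever a statistical analysis plan may say.

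**Working it through.** The point turns on no figure in the plan, so the check is an enumeration followed by a comparison of estimands.

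**1. The eight agreement pairs (Statistical analysis).** W = on-site health worker, S = on-site expert, D = distant expert.

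| Pair | Readings compared | Type | Uses consensus? |
|---|---|---|---|
| 1 | W VIA v D D-VIA | VIA v D-VIA | no |
| 2 | S VIA v D D-VIA | VIA v D-VIA | no |
| 3 | W VIA v S VIA | VIA v VIA | no |
| 4 | W VIA v W D-VIA at 3 months | VIA v D-VIA | no |
| 5 | S VIA v S D-VIA at 3 months | VIA v D-VIA | no |
| 6 | W D-VIA v S D-VIA, both at 3 months | D-VIA v D-VIA | no |
| 7 | W D-VIA at 3 months v D D-VIA | D-VIA v D-VIA | no |
| 8 | S D-VIA at 3 months v D D-VIA | D-VIA v D-VIA | no |

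The consensus appears in 0 of 8. Pairs 1, 2, 4 and 5 (four of eight) match the stated secondary outcome. Only pair 1 sets the worker's VIA against the distant expert.

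**2. The accuracy paragraph.** It covers the smartphone diagnosis against histology. Neither the consensus nor the worker's VIA is named, so even the comparison with conventional VIA announced in the Abstract is not written down as an accuracy analysis.

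**3. What each contrast estimates.** Let W, E and C be the calls of the worker, the distant expert and the consensus. Among women with histological CIN2+:

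- Assisting: Se(C) − Se(W) = P(W−, C+) − P(W+, C−)
- Replacing: Se(E) − Se(W) = P(W−, E+) − P(W+, E−)

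The two differ by Se(E) − Se(C). This is zero if the consensus always follows the expert, or if its departures happen to cancel. The same identity holds for specificity among the remaining women. Nothing planned estimates any term containing C.

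McNemar's test on pair 1 compares P(W−, E+) with P(W+, E−) over all women, with and without disease. A shift in positivity there may be a gain in sensitivity, a loss of specificity, or both.

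**4. Can an indirect answer be had?** Yes. Worker VIA and distant D-VIA are read in the same women, and Study procedure states biopsies and curettage without limiting them to VIA-positive women. Se(E) − Se(W) and its specificity counterpart can be computed, although the plan does not list them.

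**5. Timing.** The Abstract speaks of later evaluation of the images, the Introduction of real-time advice, Study procedure of treatment at the same visit, and the Flowchart joins consensus and management in one label. Together these do not settle whether the consensus is reached before or after the decision it might assist.

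**6. Sample size, checked for completeness.** The 8% v 4% assumption concerns D-VIA v VIA, so it points to the replacement contrast. The stated 1000 was not reproduced. Two independent groups (two-sided 0.05, 80% power) need 553 per group, 1106 in all. The paired formula n = (z_a√p_d + z_b√(p_d − d²))²/d² with d = 0.04 gives 194 if the worker's detections are nested in the expert's (p_d = 0.04) and 555 if the readings are independent (p_d = 0.1136). The discordance p_d is an assumption, because the protocol gives none. This is a separate matter and the present point does not depend on it.

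**The case against.** The strongest reply is that the wording of primary outcome 2 does not mention consensus. Read with the Abstract and the sample-size assumption, improvement of VIA can mean D-VIA against VIA with histology as reference, and the data for that are all planned. Improvement could also mean learning over time, which the Flowchart mentions. The list of eight is one of agreement between assessors; a joint consensus is not an assessor, and its agreement with either contributor would be partly built in. A statistical analysis plan, not shown here, might add the rest.

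Much of this stands. It rules out four stronger conclusions that a reader might infer:

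- **That the objective cannot be answered, or that neither primary outcome has any estimate.** An indirect answer to outcome 2 is available. Outcome 1 names no distant expert, and pair 4 bears on it.
- **That the trial reports its secondary outcome eight times over.** Only four of the eight pairs are that outcome.
- **That the consensus comes too late to affect treatment.** This would rest on one flowchart label whose layout is not available, and the Introduction speaks of real-time advice. The text is unclear on the order; it does not show it.
- **That the loss can be sized from the plan's 4% and 8%.** An assisted yield somewhere between those two figures only restates an assumption of nested detections, and it ignores false positives.

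What does not stand is that the gap is harmless. The consensus is the only described way in which the expert's reading reaches the worker for the woman concerned. The accuracy paragraph omits even the worker's VIA. A later plan can add an analysis, but not a variable that was never recorded.

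**Conclusion.** The point holds in limited form. Primary outcome 2 has no direct analysis: 0 of 8 agreement pairs and no accuracy analysis use the consensus diagnosis, and the accuracy paragraph does not name the worker's VIA. The planned data allow an indirect contrast of distant D-VIA with worker VIA against histology, but it measures substitution of one reader for another. It equals the effect of assistance only under the assumption that the consensus follows the expert throughout, or departs from the expert in ways that cancel.

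The conclusion rests on reading the consensus as the vehicle of improvement, which Study procedure and the Flowchart support but the Objective section does not spell out. No numerical loss can be derived from the protocol. The matter should be fixed before recruitment; it does not make the study uninterpretable.

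**What to change.** 1. Lock the worker's initial VIA result on the online platform before any feedback from the distant expert.
2. Record the consensus diagnosis as its own dated field, before histology is known.
3. Extend the accuracy analysis with two paired comparisons against histology: worker VIA v consensus, and worker VIA v distant D-VIA. Report the difference in sensitivity among women with CIN2+ and in specificity among the rest, with the numbers of calls changed correctly and incorrectly. Name the first as the analysis of primary outcome 2.
4. Keep the eight agreement pairs as secondary.
5. Reconcile the Abstract, Introduction, Study procedure and Flowchart on whether consensus precedes or follows same-visit treatment, and record the order for each woman. Which order applies is for the investigators to state.

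The cost is one data field (with its date and order) and one extra analysis. The consensus discussion is already planned, so no new readers, visits or procedures are needed. On the plan's own assumption, 8% of 1000 is 80 women with CIN2+ detected by D-VIA. If these are confirmed by histology, the sensitivity comparison would rest on at least that many women, and it should be reported with confidence intervals.
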